### Mixed Methods Integration

The study adopts a sequential explanatory mixed methods design, wherein qualitative findings from phase 1 inform the quantitative evaluation in phase 3. Integration of findings is achieved through the use of joint interpretive displays, which link CCCM content domains with corresponding subscales of the CCAT-N. This approach enables the generation of comprehensive metainferences by combining statistical outcomes with experiential insights related to intervention implementation.

### Planned Data Analysis

Quantitative analysis for phase 3 will focus on evaluating the effectiveness of the CCCM intervention. The primary outcome, namely, cultural competence as measured by total CCAT-N scores, will be analyzed using linear mixed-effects models, incorporating random intercepts to account for clustering at the ward level.

Secondary outcomes will be analyzed using generalized estimating equations to assess changes over time across baseline, postintervention, and 90-day follow-up measurements. Mediation analysis will also be conducted to examine whether improvements in cultural competence mediate changes in patient satisfaction.

Missing data will be handled using multiple imputation methods, provided that missingness does not exceed 20%, and patterns of missing data will be carefully examined prior to analysis.

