**Methods:**

This 3-phase parallel-group RCT is being conducted in the medical-surgical wards of the Acharya Vinoba Bhave Rural Hospital, Wardha, Maharashtra, India (2024-2026). In phase 1 (completed), the CCCM was developed via thematic analysis of 20 interviews with nurses, educators, and patients. In phase 2 (completed), the CCCM and a patient satisfaction tool were validated using a 2-round Delphi process involving 15 experts (CCCM: content validity index ≥0.89; patient satisfaction tool: Cronbach α=0.87-0.92). Phase 3 is ongoing: 55 nurses are randomized in a 1:1 ratio to either the CCCM (5×1-hour sessions+boosters) or routine care. The primary outcome is the postintervention Cultural Competence Assessment Tool for Nurses score, while secondary outcomes include subscales, patient satisfaction, and 90-day retention. The sample size is calculated using G*Power based on an anticipated effect size of 0.82. Participants are randomly allocated through computer-generated block randomization stratified by seniority, and outcome assessors and data analysts are blinded to group allocation. Data will be analyzed using SPSS (intention-to-treat, linear mixed-effects models; *P*<.05). Patient satisfaction outcomes will be evaluated using data from 120 patients.

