### Randomization and Blinding

Participants are randomly assigned in a 1:1 ratio to the intervention or control group using a block randomization approach with stratification by ward seniority (junior vs senior nurses). Allocation concealment is ensured using sequentially numbered, opaque, sealed envelopes prepared independently before enrollment. Blinding of participants is not feasible due to the nature of the educational intervention. However, outcome assessors and data analysts remain blinded to group allocation. To reduce contamination, training sessions are conducted during off-duty hours, intervention materials are restricted to the intervention group, and patient allocation is organized after completion of training. The control group is offered access to the CCCM after study completion.

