### Data Analysis

Data analysis is conducted to compare outcomes between the intervention and control groups. Descriptive statistics are used to summarize baseline characteristics and outcome variables. Baseline comparability between groups is assessed prior to outcome analysis. For the primary outcome, postintervention CCAT-N scores are compared between groups using a 2-tailed independent samples *t* test. Where baseline differences are present, analysis of covariance is applied to adjust for baseline values. Changes in outcomes over time are analyzed using repeated measures analysis of variance or mixed-effects modeling to account for within-participants variability. Both intention-to-treat and per-protocol analyses are performed to ensure robustness of findings. Missing data are addressed using multiple imputation methods. For patient satisfaction outcomes, either parametric or nonparametric statistical tests are applied depending on data distribution. Subgroup analyses are conducted to explore potential effect modification based on ward seniority. A 2-tailed *P* value of <.05 is considered statistically significant.

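### The primary outcome is given a t test with an undefined switch to ANCOVA in one section and a ward-intercept mixed model in another, so the primary P value is not uniquely defined

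*Protocol article*

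**What the plan says.** The abstract fixes the endpoint: "The primary outcome is the postintervention Cultural Competence Assessment Tool for Nurses score". It gives the method for the trial as a whole: "Data will be analyzed using SPSS (intention-to-treat, linear mixed-effects models".

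The Data Analysis section in Methods says: "For the primary outcome, postintervention CCAT-N scores are compared between groups using a 2-tailed independent samples" t test. It then adds a conditional step: "Where baseline differences are present, analysis of covariance is applied to adjust for baseline values". It gives no threshold, test or other criterion for a baseline difference. A later sentence covers trajectories: "Changes in outcomes over time are analyzed using repeated measures analysis of variance or mixed-effects modeling".

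The Planned Data Analysis section in Results returns to the primary outcome, total CCAT-N, and says that it "will be analyzed using linear mixed-effects models, incorporating random intercepts to account for clustering at the ward level". It lists no fixed effects.

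Randomization and Blinding describes a "block randomization approach with stratification by ward seniority (junior vs senior nurses"). In the stated analyses seniority appears only as a subgroup factor.

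Both analysis sections are current text. Neither is called a sensitivity analysis, and neither refers to the other.

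**The concern.** A confirmatory trial needs one analysis that produces the primary P value. Here three routes are written down for the same score: the unadjusted t test, ANCOVA under an undefined condition, and a mixed model with a ward intercept. They use different information and can disagree on the same data. If they do, the text does not say which one decides.

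Keeping analysts blind to allocation does not settle this, because a two-sided P value is the same whichever arm carries which label. The smaller value could be picked without knowing the arms.

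The conditional ANCOVA has its own fault. Whether to adjust for baseline is decided after looking at baseline, and the criterion is left open. The t test also ignores the factor that balanced the randomization.

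**Working it through.** **1. Which analysis underlies the sample size.** Inputs from Sample Size Determination: d about 0.8, two-sided alpha .05, power 90%. The exact noncentral t calculation gives 33.8, so 34 per group, which is the stated minimum. The sample size therefore rests on the two-sample t test, while the abstract and Planned Data Analysis name mixed models.

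**2. Assumptions for the error rates.** Analysed n is 55 × (1 − 0.20) = 44 per arm, from the stated final size and attrition. The documents give no ward ICC and no pre-post correlation r. I take ICC 0 to 0.10 and r = 0.5, 0.7 and 0.82. The last value is borrowed from the 14-day test-retest figure for CCAT-N, which is not a pre-post correlation in the trial.

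**3. t test against ward model.** Null simulation with 44 per arm, 6 wards, postintervention score only and a random ward intercept (4,000 replicates). Share of trials in which the smaller P value is below .05:

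| ICC | Type I error |
|---|---|
| 0 | 5.0% |
| 0.05 | 5.6% |
| 0.10 | 6.0% |

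The simulation standard error near 5% is √(0.05 × 0.95 / 4,000) = 0.34 percentage points. A second simulation used 110 nurses, with wards as fixed effects in place of the random intercept. There the two analyses gave opposite verdicts in 1.8%-3.2% of null trials and in 5%-10% of trials at a true d of 0.5.

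**4. t test against ANCOVA, free choice.** Let Z_y and Z_b be the standardized arm differences after the intervention and at baseline. Under the null they have correlation r. The ANCOVA statistic is, in large samples, Z_A = (Z_y − r·Z_b) / √(1 − r²). Its correlation with Z_y is √(1 − r²), and it is independent of Z_b. The error rate is 1 − P(|Z_y| < 1.96 and |Z_A| < 1.96).

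| r | √(1 − r²) | Formula | Simulated, 44 per arm (two runs) |
|---|---|---|---|
| 0.5 | 0.866 | 7.3% | 7.1%, 7.3% |
| 0.7 | 0.714 | 8.3% | 8.4%, 8.0% |
| 0.82 | 0.572 | 8.9% | 8.8%, 8.9% |

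**5. The switch followed as a rule.** Assume that it is triggered by a baseline test at P<.05. Because Z_A is independent of Z_b, the error rate is 0.05 − P(|Z_y| > 1.96 and |Z_b| > 1.96) + 0.05 × 0.05.

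- r = 0.5: 0.0500 − 0.0093 + 0.0025 = 4.3%
- r = 0.7: 0.0500 − 0.0165 + 0.0025 = 3.6%
- r = 0.82: 0.0500 − 0.0232 + 0.0025 = 2.9%

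Simulation at 44 per arm gave 4.3%, 3.5% and 2.6%-2.9%. The rule misses 5% on the conservative side.

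**6. Seniority and baseline.** In the 110-nurse simulation (4,000 replicates, r = 0.5, ICC 0-0.10), the share of outcome variance due to seniority was an assumption.

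| Share | t test, actual alpha | With stratum |
|---|---|---|
| 0 | 5.4% | 5.4% |
| 0.05 | 4.4% | 5.3% |
| 0.10 | 4.1% | 5.4% |
| 0.25 | 2.4% | 5.1% |

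At d = 0.5 and a share of 0.25, adding the stratum to the t test comparison raised power from 78% to 86%. With no ward or seniority effect, always adjusting for baseline raised it from 75% to 85%.

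**The case against.** The strongest reply is that the text allows less freedom than this suggests. The abstract and Planned Data Analysis both point to mixed models, so a reader might take the mixed model as primary. Data Analysis does not offer ANCOVA as a free alternative but ties it to a condition. An unseen analysis plan may settle the order and the covariates.

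Part of this stands. The 7-9% figures describe an unrestricted choice between the t test and ANCOVA. A reader might carry them over to the t test and ward model, but for that pair the figure is about 5-6%. The ANCOVA switch, followed as a baseline significance test, is conservative. None of these figures shows that anyone would choose by P value.

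Two further readings are tempting and not supported:

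- **That the missing seniority term makes the P value non-unique.** It does not. Leaving out a stratum is a separate and lesser matter of precision. It can be shown only for the t test, because Planned Data Analysis lists no fixed effects for its model.
- **That the mixed model wrongly omits correlation within nurse.** The abstract defines the primary outcome as a single postintervention score, for which a nurse effect is not needed. Where Data Analysis does model change over time, it says that within-participant variability is accounted for.

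The reply does not remove the contradiction. An analysis plan could agree with only one of the two sections, so one of them misstates the primary analysis.

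**Conclusion.** The point holds as a contradiction about the primary result. Three routes to the primary P value are written down, one of them data-dependent with no criterion, and nothing ranks them.

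The consequence is real but moderate. Depending on which routes are compared, type I error runs from about 5-6% (t test or ward model) to 7-9% (t test or ANCOVA), and it falls to about 2.6-4.3% if the ANCOVA switch is followed as a baseline test at P<.05. All of this rests on 44 analysed nurses per arm and on assumed ICCs and correlations. The contradiction itself needs no assumption.

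The t test's neglect of seniority is a secondary point. It costs power and makes the test conservative if seniority predicts CCAT-N, and it does not inflate type I error.

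**What to change.** State one primary analysis in the same words in the abstract, Data Analysis and Planned Data Analysis: a linear model of the postintervention CCAT-N score with arm, baseline CCAT-N and seniority stratum as fixed effects, and the random ward intercept that is already planned. Baseline CCAT-N is always included, whatever imbalance is observed, and the baseline-difference trigger is deleted. Label the unadjusted t test as a sensitivity analysis. Keep the 90-day and change-over-time analyses secondary.

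The cost is small but more than an edit. Baseline CCAT-N and seniority are already collected, and ward is already in the planned model, so no new data are needed. However, the implementation status places the immediate postintervention assessments in November 2025, and final analysis is expected between March and June 2026. The choice therefore has to be recorded in a dated amendment before any unblinded analysis. Made later, it could not credibly be called prespecified.

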### Qualitative Follow-Up Component

A qualitative component is planned as part of the mixed methods design to further explore participant experiences. Follow-up interviews will be conducted with a purposive sample of 15 nurses and 15 patients. Data will be analyzed using reflexive thematic analysis, with explicit attention to researcher positionality and iterative development of the coding framework.

Trustworthiness of qualitative findings will be ensured using the criteria proposed by Lincoln and Guba [18], including credibility, transferability, dependability, and confirmability. Participant validation will also be undertaken to enhance the authenticity of findings.

### Projected Timeline and Dissemination

The final statistical analysis is expected to be completed between March and June 2026. The findings of the study will be disseminated through peer-reviewed journals focusing on transcultural nursing, nursing education, and health care quality. In addition, the results will be presented at national and international conferences to facilitate wider academic and clinical engagement. Efforts will also be made to share key findings with health care institutions and nursing educators to support the integration of culturally competent practices into clinical training and practice.

## Discussion

### Anticipated Findings

This 3-phase trial hypothesizes that the CCCM will produce moderate-to-large improvements in nurses’ cultural competence and patient satisfaction, consistent with structured intervention studies demonstrating moderate-to-large effect sizes [19,20].

Indian nursing curricula continue to prioritize biomedical competencies over structured transcultural development [21]. These gaps are compounded by limitations in faculty preparedness [22]. Linguistic diversity across India’s 22 officially recognized languages presents persistent communication barriers [23]. These challenges are further amplified by the growth of medical tourism [24]. The CCCM addresses these gaps through a structured 5-domain model grounded in transcultural and cultural safety frameworks [13,25]. Its blended instructional design aligns with simulation-based educational evidence demonstrating superior competency gains [19].

Compared with previous evidence from quasi-experimental studies conducted in Indian hospitals [26] and recent RCTs [19], this protocol incorporates CONSORT (Consolidated Standards of Reporting Trials)–aligned randomization (Figure 1) [27], validated psychometric development standards [28], rigorous nursing research methodology [29], structured contamination control strategies, and a 90-day follow-up period. Implementation strategies are informed by updated reach, effectiveness, adoption, implementation, and maintenance (RE-AIM) framework guidance [30]. The single-center setting reflects current migration and linguistic diversity patterns [22]. The selected outcomes are aligned with the World Health Organization’s global health equity priorities [31].

If successful, this trial will provide (1) one of the first rigorously designed RCTs in India evaluating structured cultural competence training; (2) a validated, region-specific assessment and training toolkit; (3) a scalable 5-session intervention model; and (4) an equity-oriented strategy aligned with the World Health Organization’s health equity goals [30].

**Figure 1 figure1:**
[figure not shown]
CONSORT (Consolidated Standards of Reporting Trials) 2023 flow diagram—culturally competent care module (CCCM) randomized controlled trial.

### Limitations

This study has certain limitations that should be considered when interpreting the findings. First, the trial is conducted in a single tertiary care teaching hospital, which may modestly limit generalizability to other health care settings across India that differ in infrastructure, staffing patterns, patient load, and linguistic diversity.

Second, although contamination control measures were incorporated, some degree of informal knowledge sharing between intervention and control participants in shared clinical environments cannot be entirely ruled out, which may have influenced group differences. Third, selected nurse-level outcomes are based on self-reported measures and may be subject to social desirability tendencies, despite the use of blinded outcome assessment procedures. Fourth, the 3-month follow-up period provides insight into short-term outcomes; however, longer follow-up would offer a clearer understanding of sustainability over time.

Fifth, contextual realities within Indian health care settings—including workload intensity, shift rotations, and limited protected training time—may influence implementation dynamics. These factors should be considered when adapting the intervention to other institutions. Linguistic diversity across regions may also necessitate contextual tailoring of training materials. Finally, while patient satisfaction is included as an outcome indicator, broader structural determinants of health equity extend beyond the scope of this intervention.

### Future Directions

Future research should evaluate the effectiveness of CCCM in multicenter studies involving diverse health care settings across India. Longer follow-up periods are needed to determine the sustainability of improvements in cultural competence and patient satisfaction. Further studies should also examine the implementation of the module in different clinical specialties and evaluate its adaptability to other cultural and health care contexts. In addition, implementation research could explore barriers and facilitators to integrating culturally competent training into routine nursing education and continuing professional development.

### Conclusions

This 3-phase RCT protocol outlines a rigorously designed evaluation of a structured CCCM tailored to the Indian tertiary hospital context. By integrating qualitative module development, expert validation, and a parallel-group randomized design with blinded outcome assessment and follow-up evaluation, the study addresses key methodological gaps identified in recent cultural competence intervention research.

If demonstrated to be effective, the CCCM may provide evidence for a pragmatic, time-efficient, and contextually adapted cultural competence training model capable of improving nurse-level competencies and patient satisfaction outcomes. Given India’s increasing sociolinguistic diversity and expanding international patient population, structured cultural competence training represents both an equity-oriented strategy and a quality improvement initiative. The findings may inform curriculum reform, institutional training policies, and future multicenter effectiveness-implementation hybrid studies.

## Data Availability

Data will be generated and analyzed during phase 3 of this randomized controlled trial. Deidentified participant-level data, including cultural competence scores and patient satisfaction outcomes, will be made available upon reasonable request from the corresponding author following completion of the study and publication of the primary results. Data sharing will be subject to approval by the Institutional Ethics Committee and in accordance with institutional data protection policies to ensure participant confidentiality. Where feasible, aggregated datasets and supporting materials may be made available through publicly accessible repositories or as supplementary files accompanying the publication. Requests for access to the data should include a clear research proposal and will be considered on a case-by-case basis.

## Appendix

Multimedia Appendix 1 Cultural Competence Assessment Tool for Nurses.

Multimedia Appendix 2 Interview format.

## Abbreviations

ASKED: awareness, skills, knowledge, encounter, desire
CCAT-N: Cultural Competence Assessment Tool for Nurses
CCCM: culturally competent care module
CONSORT: Consolidated Standards of Reporting Trials
CVI: content validity index
RCT: randomized controlled trial
